### Random assignment and blinding

2.6

Following baseline assessments, participants will be randomly assigned in a 1:1 ratio to either the AE group or the Con group. The randomization sequence will be generated using a computer-based random number generator (Microsoft Excel) by an independent statistician who is not involved in participant recruitment or data collection, employing a simple randomization method. Allocation concealment will be maintained using sequentially numbered, opaque, sealed envelopes. These envelopes will be kept by a designated research assistant and will be opened only after baseline assessments are completed, thereby minimizing selection bias.

This study employs a single-assessor-blind design. To maintain the blind, a rigorous single-blinded assessor design will be implemented where all participants are assigned unique alphanumeric identification codes for data collection and analysis. Specifically, imaging specialists (echocardiographers and vascular technicians) will perform scans and post-processing analyses using only these codes, and will be strictly trained to refrain from discussing intervention allocation or personal perceptions of improvement with participants during examinations to prevent inadvertent unblinding. Similarly, biochemical analysts will process blood samples labeled solely with identification codes, ensuring they remain unaware of group allocation or sampling time points. Furthermore, statistical analysis will be conducted by an independent statistician using de-identified datasets with dummy group labels. Access to unblinded data will be restricted exclusively to the clinical exercise physiologists delivering the intervention and the Data Safety Monitoring Board responsible for monitoring adverse events. This design ensures methodological rigor, minimizes bias, and enhances the reliability and validity of the study findings.

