Participants assigned to the control group (Con group) will not receive any supervised or structured exercise intervention. To ensure a clear distinction from the AE group, they will be explicitly instructed to maintain their habitual lifestyle patterns throughout the 12-week study period. To objectively monitor adherence to these instructions, physical activity levels will be assessed weekly using the International Physical Activity Questionnaire (IPAQ). Any deviations from baseline activity patterns will be documented.

Throughout the 12-week intervention, all participants will be required to maintain their baseline medication regimens. Dosage adjustments will be permitted only when medically necessary for safety reasons (e.g., in cases of severe hypoglycemia or uncontrolled blood pressure), and any such modifications will be meticulously documented.

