### Measurement

2.8

Comprehensive clinical assessments—including metabolic, cardiovascular, cardiopulmonary, fatigue, and skeletal muscle tests—will be performed at baseline and at the 12-week follow-up. With the exception of the oral glucose tolerance test and associated 2-hour postprandial glucose measurement, all assessments will be conducted in the morning after a minimum 12-hour overnight fast. Participants will be instructed to abstain from alcohol, caffeine for 24 hours and withhold their morning medications on the day of assessment to minimize pharmacological interference. To mitigate the confounding effects of acute exercise, post-intervention assessments will be scheduled 48 hours after the final training session. For biochemical analyses, venous blood samples (approximately 6 mL) will be drawn from an antecubital vein into serum separation tubes. The tubes will be gently inverted and then allowed to clot at room temperature for 30–60 minutes. The samples will then be centrifuged at 3000 rpm for 10 minutes at 4°C, and the resulting serum will be aliquoted and stored at –80°C until analysis. To minimize inter-assessor and instrument variability, all measurements will be performed by the same trained technician using the same equipment at both time points.

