#### Speckle-tracking and myocardial work analysis

2.10.2

Two-dimensional echocardiographic images of the left ventricle—including short-axis views at the basal, mid, and apical levels, as well as apical four-chamber, two-chamber, and three-chamber views—will be analyzed using EchoPAC software (Version 203). Post-processing will be performed to obtain left ventricular global longitudinal strain (LS), circumferential strain (CS), radial strain (RS), and rotational/torsional angles. Brachial artery pressure values recorded before imaging will be entered into the software, which will automatically generate left ventricular pressure–strain loops and calculate myocardial work parameters, including global work index (GWI), global constructive work (GCW), global wasted work (GWW), and global work efficiency (GWE).

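### The imaging role that scans the unblinded participants also post-processes their images under the same participant code, so the code masks the reader neither to visit nor to a disclosed allocation

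*Protocol article*

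**What the plan says.** Section 2.6 (Random assignment and blinding) states: "This study employs a single-assessor-blind design". It explains the mechanism: "all participants are assigned unique alphanumeric identification codes for data collection and analysis", and "imaging specialists (echocardiographers and vascular technicians) will perform scans and post-processing analyses using only these codes". The safeguard during the examination is that these specialists "will be strictly trained to refrain from discussing intervention allocation or personal perceptions of improvement with participants during examinations".

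The same section gives the laboratory analysts a stronger form of masking, with samples carrying only codes, "ensuring they remain unaware of group allocation or sampling time points". No time-point masking is stated for imaging.

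Section 2.8 (Measurement) adds that "all measurements will be performed by the same trained technician using the same equipment at both time points".

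Section 2.7 (Intervention) says that control participants "will not receive any supervised or structured exercise intervention", so every participant knows which arm they are in. Both primary outcomes, NMD (section 2.10.1) and GWE (section 2.10.2), are imaging measurements.

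**The concern.** In an exercise trial neither participants nor trainers can be blinded, so the assessor's blinding is the main protection against detection bias. An identification code gives that protection only when the reader has not met the person behind it. Here the role that meets the participant under a code also post-processes the images under that code, and anything learned in the examination room can be carried over to the reading. The training binds staff; as described, it does not address a participant who mentions the exercise sessions unprompted.

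Time point is a separate matter and needs no disclosure. A technician who measures at both visits knows which visit is which, and a reader who knows the visit may expect change.

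As a result, the two primary outcomes have weaker stated masking than the serum markers. If knowledge of allocation influenced post-processing, the effect would fall directly on a co-primary comparison.

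**Working it through.** The plan gives no figure for this point, so there is none to reproduce. The check has two parts.

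**1. The stated workflows side by side**

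| Feature | Imaging (NMD, GWE) | Blood markers |
|---|---|---|
| Meets the participant under the code | Yes: the role scans | The analysts work from coded samples |
| Produces the outcome value under the code | Yes: the same role post-processes | Yes |
| Stated masking to group | Codes, plus training of staff not to discuss | Codes |
| Stated masking to time point | None; same technician at both visits | Yes |

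The code can do its work for the blood analysts. For imaging it cannot hide the visit, and it hides the group only as long as the participant does not reveal it.

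**2. What a given bias would do (illustration for GWE)**

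Inputs:
- SD 4.0 and planned difference 2.7 points (section 2.5).
- Per arm, 37 recruited less the planned 10% dropout: 37 × 0.9 = 33.3, taken as 33.
- Net between-arm shift b = share of participants who disclose × shift in an affected reading. The documents give neither factor, so both are assumed.

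Standard error of the difference: 4.0 × √(2/33) = 0.985 points.

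With no true effect, the rejection rate of a two-sided 5% test is P(|Z + b/0.985| > 1.96), by normal approximation.

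| Assumed share × shift | b (points) | b as share of 2.7 | b/0.985 | Error rate |
|---|---|---|---|---|
| 20% × 1.0 | 0.2 | 7% | 0.20 | about 5.5% |
| 50% × 1.0 | 0.5 | 19% | 0.51 | about 8% |
| 100% × 1.0 | 1.0 | 37% | 1.02 | about 17% |

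The last row requires every participant to disclose and every reading to move by a full point. It is the top of the range shown and not an expected value. No corresponding calculation is offered for NMD, because the documents describe too little of how the diameter is read to suggest where reader judgement would enter.

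**The case against.** A reader might infer that the individual who scans a participant is the one who reads that participant's images. The text does not say so. Section 2.6 names a plural role covering two kinds of specialist, and section 2.8 fixes the technician across visits to limit variability between assessors; it does not link scanner to reader. That objection stands, and the point is worded at the level of the role.

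A reader might also infer that blinding has failed, or that nothing prevents disclosure. The documents do not support that either. Section 2.2 says the assessors are blinded and puts exercise at a fitness and rehabilitation center and assessments at a partner hospital and laboratories. Section 2.6 restricts unblinded data to the exercise physiologists and the monitoring board. Volunteered disclosure is then the main remaining route to knowledge of the group. A condensed article may also omit an instruction to participants that the full protocol contains, so its absence is not counted here as a fault.

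Section 2.10.2 says the software generates the pressure–strain loops and the work indices automatically, which narrows the room for reader influence. It does not close it: strain is first obtained by post-processing, and pressures are entered by hand or by file. The article does not describe the individual reader steps, so how much discretion they leave is not known.

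The point that survives all of this rests on a stated workflow and not on silence: one role scans and post-processes, under one code, with the same technician at both visits, while the blood analysts have masking that imaging lacks.

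**Conclusion.** The concern holds as a weakness in the stated blinding of the primary outcomes, most clearly for GWE. Under the workflow described, the participant code does not mask the imaging role to time point, and does not mask it to allocation if a participant discloses it.

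The size of any bias is unknown. The error rates of about 5.5%, 8% and 17% depend on assumed disclosure shares and reading shifts, on the planning SD of 4.0 applying to the quantity compared, and on about 33 completers per arm. It would be wrong to read the 17% as a forecast. Nor is this a contradiction or a miscalculation in the plan. It is a design choice that can be strengthened cheaply while recruitment is still under way. If scanning and reading are already done by different people, with the reader masked to visit, a sentence saying so would settle the matter.

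**What to change.** Separate reading from scanning for GWE, using the staff already in place:

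1. Keep the echo loops, which section 2.11.7 already says are stored, together with the brachial pressures recorded before imaging.
2. Have someone on the team who does not read images, such as the research assistant or the independent statistician, re-label loops and pressures with new random codes that hide participant and visit. That person holds the key.
3. After the last week-12 visit, have the existing specialists post-process all baseline and week-12 loops in random order. This keeps the same readers and equipment across visits, as section 2.8 intends.
4. Do the same for NMD only if the device stores images that can be read again; the article does not say whether it does.
5. Instruct participants not to mention their group at assessments, if the full protocol does not already do so.

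The cost is the re-labelling work, custody of the key, and GWE values that become available only after the batch read. No new scans or visits are needed. The change does not remove bias that arises while images are acquired or while the pressure that feeds GWE is measured, since both remain face to face.

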### Intervention

2.7

The exercise intervention for the AE group is structured according to the FITT-VP principle (Frequency, Intensity, Time, Type, Volume, Progression). The protocol aligns with the American College of Sports Medicine (ACSM) guidelines for exercise in patients with T2DM (23). All training sessions will be supervised by certified clinical exercise physiologists. Considering the significant effects of AE on glucose homeostasis, all supervised sessions will be scheduled 1–2 hours postprandially to prevent exercise-induced hypoglycemia.

The exercise intervention consists of a 12-week supervised program with three sessions per week. Each session comprises a 5-minute warm-up (50%–60% of HR_peak_), 50 minutes of aerobic exercise (55%–75% of HR_peak_), and a 5-minute cool-down (50%–60% of HR_peak_). Given the progressive nature of cardiorespiratory adaptations to exercise training, the 12-week program will be divided into an initial phase (Weeks 1–6) and a secondary phase (Weeks 7–12). Cardiopulmonary exercise testing (CPET) will be performed at baseline and at the end of Week 6 to assess cardiorespiratory fitness and to prescribe exercise intensity based on the heart rate peak (HR_peak_). The HR_peak_ is identified as the heart rate corresponding to the achievement of VO_2peak_ during the CPET. For participants receiving heart rate–modulating medications (e.g., β-blockers or non-dihydropyridine calcium channel blockers) or those exhibiting chronotropic incompetence with a blunted heart rate response, exercise intensity will be prescribed using a combination of the power output (Watts) derived from the CPET and the Borg Rating of Perceived Exertion (RPE; target range 12–14). This approach ensures the delivery of a consistent and relatively moderate-intensity training stimulus. Throughout the intervention, participants in the AE group will wear heart rate monitors Polar H7 (Polar Electro, Kempele, Finland) to facilitate real-time monitoring and dynamic adjustment of exercise intensity.

Participants assigned to the control group (Con group) will not receive any supervised or structured exercise intervention. To ensure a clear distinction from the AE group, they will be explicitly instructed to maintain their habitual lifestyle patterns throughout the 12-week study period. To objectively monitor adherence to these instructions, physical activity levels will be assessed weekly using the International Physical Activity Questionnaire (IPAQ). Any deviations from baseline activity patterns will be documented.

Throughout the 12-week intervention, all participants will be required to maintain their baseline medication regimens. Dosage adjustments will be permitted only when medically necessary for safety reasons (e.g., in cases of severe hypoglycemia or uncontrolled blood pressure), and any such modifications will be meticulously documented.

### Measurement

2.8

Comprehensive clinical assessments—including metabolic, cardiovascular, cardiopulmonary, fatigue, and skeletal muscle tests—will be performed at baseline and at the 12-week follow-up. With the exception of the oral glucose tolerance test and associated 2-hour postprandial glucose measurement, all assessments will be conducted in the morning after a minimum 12-hour overnight fast. Participants will be instructed to abstain from alcohol, caffeine for 24 hours and withhold their morning medications on the day of assessment to minimize pharmacological interference. To mitigate the confounding effects of acute exercise, post-intervention assessments will be scheduled 48 hours after the final training session. For biochemical analyses, venous blood samples (approximately 6 mL) will be drawn from an antecubital vein into serum separation tubes. The tubes will be gently inverted and then allowed to clot at room temperature for 30–60 minutes. The samples will then be centrifuged at 3000 rpm for 10 minutes at 4°C, and the resulting serum will be aliquoted and stored at –80°C until analysis. To minimize inter-assessor and instrument variability, all measurements will be performed by the same trained technician using the same equipment at both time points.

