We hypothesize that a 12-week moderate-intensity aerobic exercise intervention will significantly enhance integrated cardiovascular function, specifically by improving GWE and NMD, while concurrently restoring systemic energy metabolism and metabolic flexibility in patients with T2DM. Furthermore, regarding the mechanisms of fatigue alleviation, we hypothesize that aerobic exercise will mitigate fatigue via a dual pathway: centrally, by modulating the balance of neurotransmitters (including serotonin, dopamine, and GABA), and peripherally, by reducing skeletal muscle injury biomarkers (CK and Myoglobin) and oxidative stress.

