#### Oral glucose tolerance test

2.11.3

Venous fasting blood samples will be collected the following morning to avoid prolonged fasting that could lead to reactive hyperglycemia and interfere with diagnostic accuracy. A glucose solution will be prepared by dissolving 75 g of anhydrous glucose powder in 150 mL of water, and participants will be instructed to consume the entire 150 mL solution within 5 minutes. The start of ingestion will be recorded as time zero. Venous blood samples will then be collected at fasting, 60 and 120 minutes after ingestion to assess blood glucose changes.

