#### Energy metabolism

2.11.5

One hour after consuming a standardized meal, participants will undergo a 30-minute resting respiratory exchange ratio (RER) test using a metabolic gas analyzer (Cortex Meta Max 3B, CORTEX, Germany) while lying supine. The mean RER will be calculated after excluding data from the first and last 5 minutes. Subsequently, participants will perform 30 minutes of AE at 60% of their individual VO_2_peak to measure exercise RER. During the test, workload will be adjusted based on oxygen consumption to ensure the target intensity is maintained. Metabolic flexibility will be evaluated using the difference between exercise and resting RER (
ΔRER=RER_exercise−RER_rest), with a larger ΔRER indicating greater metabolic flexibility.

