#### 24-hour movement behavior

2.11.14

24-hour movement behavior will be objectively monitored using a triaxial accelerometer (ActiGraph GT3X, USA) worn on the non-dominant wrist. The sampling frequency of the accelerometer will be set to 30 Hz with a recording epoch of 10 seconds. Participants will be instructed to maintain their usual daily routines (e.g., studying, household activities, and leisure activities) and wear the device continuously throughout the monitoring period.

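### The fasting rule in section 2.8 should exempt the post-meal RER test (minor wording correction), and any CPET done fasted should be preceded by a routine glucose check (cheap safety improvement)

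*Protocol article*

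**What the plan says.** Section 2.8 (Measurement) covers the baseline and 12-week assessments and names metabolic and cardiopulmonary tests among them. Its rule is that "all assessments will be conducted in the morning after a minimum 12-hour overnight fast". The only carve-out is "With the exception of the oral glucose tolerance test and associated 2-hour postprandial glucose measurement". Participants are also told to "withhold their morning medications on the day of assessment", with the stated aim of limiting drug interference.

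Section 2.11.5 (Energy metabolism) sets a different state for one of these tests: "One hour after consuming a standardized meal, participants will undergo a 30-minute resting respiratory exchange ratio (RER) test". An exercise leg of 30 minutes at 60% of individual VO2peak follows. The difference between exercise and resting RER is the measure of metabolic flexibility, "with a larger ΔRER indicating greater metabolic flexibility".

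Section 2.11.15 describes CPET as an incremental cycle test continued to volitional exhaustion and sets no meal timing. Section 2.7 schedules supervised training 1–2 hours after eating, to prevent hypoglycaemia during exercise. Section 2.9 requires a health screen before every training session and every CPET, but measures capillary glucose only if the participant reports suggestive symptoms or general malaise.

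**The concern.** There are two separate points, and both arise from the breadth of the fasting sentence.

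The first is a conflict of wording. Nobody can be at least 12 hours fasted and one hour past a meal at the same time, and the RER test is not in the exemption. RER depends on what has recently been eaten, and metabolic flexibility is part of the trial's hypothesis (Introduction: "while concurrently restoring systemic energy metabolism and metabolic flexibility in patients with T2DM"). The prandial state for this test should therefore be stated once and consistently.

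The second is a safety point, not a contradiction. If the fasting rule is applied to CPET, the hardest effort in the trial is made without the meal that the protocol uses as its safeguard for milder exercise, and no routine glucose measurement takes its place. What is at stake is an out-of-range glucose that goes unnoticed before a test to exhaustion in a participant without symptoms.

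**Working it through.** The point is textual. The plan gives no figure to reproduce, and no power or error-rate calculation applies.

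**RER test**

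1. General rule (2.8): a fast of at least 12 hours for all assessments, with the glucose tolerance test and its 2-hour value as the only exceptions.
2. Specific rule (2.11.5): the resting measurement starts 1 hour after a standardized meal.
3. Taken literally, the two rules cannot both hold for this test.
4. The specific rule is almost certainly the intended one. It describes the procedure itself. The general sentence cannot be fully literal either, since it would also cover the activity monitor in 2.11.14, whose wearers must "wear the device continuously throughout the monitoring period".
5. The two fit together as a sequence: overnight fast, standardized meal, resting RER at 1 hour, exercise leg. The only thing missing is an exemption in 2.8.

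**CPET**

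1. Section 2.8 includes cardiopulmonary tests and does not exempt CPET. Section 2.11.15 gives no meal timing that would override it. As written, the baseline and week-12 CPETs fall under the fast. Section 2.8 says nothing about the week-6 CPET, so nothing is concluded about that test.
2. Section 2.9 postpones a session if measured glucose is below 3.9 mmol/L, above 16.7 mmol/L, or above 13.9 mmol/L with ketonuria or symptoms of decompensation. These limits need a measured value, and the measurement is triggered only by symptoms or malaise. In a participant who feels well, no limit can act.
3. The blood drawn for fasting glucose does not fill the gap. Section 2.8 has serum stored at –80°C until analysis, and 2.11.1 refers back to that procedure. The article does not make the draw a pre-test check.
4. The upper limits matter as well as the lower one, because section 2.3 admits participants with HbA1c up to 11.0%.
5. Comparison with training. A training session lasts 5 + 50 + 5 = 60 minutes, with the main part at 55–75% of peak heart rate. A CPET has a 3-minute warm-up (50 W for men), then rises 15 W per minute. The article gives no peak workload. Assuming a man stops between 125 and 170 W, the ramp lasts (125 − 50)/15 = 5 minutes to (170 − 50)/15 = 8 minutes, so the whole test takes about 8 to 11 minutes. CPET is harder than training but much shorter.

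**The case against.** On RER, the strongest reply is that the conflict resolves itself: staff running the test follow its own procedure. That stands, and it is why this is only a minor correction. A reader might go further and infer that some RER tests were done fasted and others fed, so that the metabolic flexibility result is biased. The article does not support this. Nothing in it suggests that any RER test was done fasted. The outcome is secondary and declared exploratory in 2.12, and NMD, GWE and the sample size are untouched. Nor should anything be read into the exemption of the glucose tolerance test alone, because 2.11.3 gives another possible reason for it: samples are "collected the following morning to avoid prolonged fasting".

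On CPET, three replies carry weight.

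- It is awkward to call the fasting sentence non-literal for RER and then apply it to CPET. The difference is that RER has its own meal rule and CPET has none. Even so, the exercise RER leg is set from VO2peak, so a CPET result must already exist by then. Testing is therefore sequenced in a way that the article does not lay out. That CPETs are in practice run fasted is a fair reading but not a certain one.
- The meal rule in 2.7 is written for hour-long training and does not transfer automatically to a short test. This weakens the comparison without removing it.
- Section 2.9 is a deliberate rule with mandatory screening, treatment and re-testing for hypoglycaemia, and stopping criteria, and withheld morning medication may also reduce the risk. All of this lowers the risk. None of it detects an out-of-range glucose without symptoms, and the medication instruction is not given as a safety measure.

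**Conclusion.** Both points hold at modest weight.

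The RER item is a minor correction to the exemption in 2.8. No effect on any result is shown or can be sized from the article. No audit of visit records is needed unless the sponsor has reason to think that a test was done fasted.

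The CPET item is a cheap safety improvement, conditional on CPET being done fasted. Confidence that the text places the baseline and week-12 tests after the fast is high. Confidence that they are actually run that way is moderate. A reader might infer that the protocol contradicts itself on CPET or exposes participants to a demonstrated hazard. It does neither: no rule for CPET conflicts with another, and existing safeguards already reduce the risk. What remains is that thresholds already in the protocol cannot operate in a symptom-free fasted participant before a maximal test.

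**What to change.** In section 2.8, add the RER test to the exemption and state its sequence: overnight fast, standardized meal, resting RER at 1 hour, then the exercise leg, identical at baseline and week 12. This costs one clause.

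In section 2.9, add one sentence: before any CPET done fasted, capillary glucose is measured whether or not symptoms are reported, and the existing thresholds apply (below 3.9 mmol/L, above 16.7 mmol/L, or above 13.9 mmol/L with ketonuria or symptoms). It would help to state the intended prandial state for CPET at the same time. The cost is one finger-prick per fasted test, so two per participant if both the baseline and week-12 tests are fasted, and an occasional postponed test.
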